### **The principal investigator**

- Write the protocol, design the questionnaires, with the co-investigators
- Trains teams, partners, agents, service providers in the study protocol, its tools, and quality control
- Ensures coordination between everyone and project communication with the support of ACF
- Ensures quality control at the start of the study then during the study, being present on site, sets up the monitoring of data entry, the correction if necessary, the locking up of consents, the protection of data, mutual accountability of all to obtain reliable data
- Organizes coordination meetings in Mbuji Mayi between ACF, the owners of health centers and / or their representatives for the proper implementation of care and concomitant research
- Prepare monthly reports and presentations of study progress to inform study partners and decision makers
- Conducts the final statistical analyzes from the data, writes scientific articles presenting the results obtained with the partners, formulates the conclusions, and suggests operational recommendations for the PCIMA.
- Contributes to the drafting of proposals to secure additional funding
- Presents the final results to the authorities and representatives of the participants, to the international nutrition community and to the scientific community in the field.

## **The ACF Research Program Manager**

- Contributes to the study design, tools, training design
- Coordinates the study on the side of the ACF promoter: brings together the work team to build the study together, convenes the COPIL for decision-making (if temporary suspension, if fundraising, etc.)
- Ensures the possible recruitment of staff for the study
- Train study staff with the principal investigator
- Ensures the coordination between the various actors of the project: researchers, data entry agents, IT, ACF supervisors, UNTI etc. in order to seek the best continuity of care for the children and the smooth running of the study
- Contributes to data quality control, ensures supervision field visits
- Provide reporting on all meetings held by the project team
- Ensure compliance with the schedule of activities by alerting stakeholders
- Keeps the project calendar up-to-date (chronogram), the 1-page flyer for project communication, the Teams group with jointly shared documents
- Contributes to the drafting of proposals to secure additional funding
- Contributes to the writing of final scientific articles as a co-author
- Coordinates the presentation of results to the authorities between researchers and ACF, facilitates the organization of communication events as necessary

## **ACF supervisors :**

- Ensure the first quality control of the data collected in the UNTAs;
- Ensure strict adherence to the SAM treatment protocol in UNTAs;
- Inform the investigators about any anomalies observed in the UNTAs;
- Strengthen the capacities of the UNTA teams which show certain weaknesses;

## **IT in the UNTA (nurses):**

- Participate in research protocol training
- Recruit trial participants according to the inclusion criteria;
- Collect informed consents and keep them locked up before transmitting them to the principal investigator;
- Conduct medical and nutritional consultations with anthropometric measurements;
- Divide the participants into the two groups;
- Distribute RUTF to participants according to their group (control or intervention);

- Report / call by phone to find out how to manage any particular case asking questions about the research protocol, keep a debriefing time at the end of the week to share with researchers the constraints encountered and find solutions together
- Inform of any absences and replacement

**Socio-anthropological investigators** (assistants and note taker):

- Identify, with help from community relays, focus group participants and in-depth interviews;
- Obtain informed consent from participants in focus groups and in-depth interviews;
- Lead in-depth interviews and focus groups;
- Ensure note-taking during in-depth interviews and focus groups;
- Ensure the recording of in-depth interviews and focus groups with the permission of the participants; transcribe each interview into French in an anonymized Word document with unique identifying number and date, and keep the confidential register of corresponding identifiers and identities up to date
- Transmit to investigators the recordings and transcriptions made and the identification register.

**Data entry clerks (ESP):**

- Participate in the study protocol training
- Go to the health centers to enter on a tablet all the data of the study - the socio-demographic, economic and anthropometric characteristics of the participants; with respect for data confidentiality, data backup and protection procedures;
- Report any difficulty or question to the researchers to avoid making decisions alone that could affect the quality of the data, not to take initiatives on the data without the researcher's agreement and to note in a logbook all the actions carried out on the data ( corrections, modifications etc.)
- Participate in data entry coordination meetings to provide detailed feedback on errors encountered and failure to complete UNTA forms and questionnaires, to health center owners via the researcher and the research PR
- Ensure the transcription of in-depth interviews and focus groups.

## **f. Organization of the collection**

### ***At UNTA level***

On admission, if a patient meets the study inclusion criteria, the receiving provider explains how the study is going and requests informed consent to include them in the study. If consent is obtained, the nurse assigns an ID to the child that matches the randomization ID. The randomization group is not mentioned. Information on socio-demographic characteristics is collected by IT.

The provider responsible for medically examining the child and taking the anthropometric measurements examines and provides information on the measurements. Anthropometric measurements will be taken according to the PCIMA protocol once a week when the child visits the center until the cured discharge or up to 12 weeks maximum.

- PB will be measured using a PB tape on the left arm halfway between the acromion and the olecranon;
- The weight using a SECA scale depending on whether or not the child can stand up;
- The height will be measured using a wooden measuring board in the supine or upright position depending on whether the child is <24 months or ≥24 months (or ≥ 87 cm) respectively;
- Edemas will be assessed according to their importance (0; + if limited to the feet; and ++ if limited to the legs).

The medical treatment is given to the child according to what is defined in the PCIMA protocol.

Finally, the child receives the amount of RUTF planned for the week as well as health education. It is the same provider in charge of the admission who will ensure the distribution of RUTF and will know who receives the reduced dose according to the IDs of the children. This provider will not follow up on children to keep blind. Each participant receives the quantity of RUTF described in Table 1 (presented above).

All the information on the identifier, the socio-demographic characteristics and the anthropometric measurements are noted in the individual follow-up sheet of the corresponding participant.

**Assessment of psychomotor development:** Depending on the sampling interval, the evaluation of psychomotor development will be carried out on 40% of the sample size, by means of the ASQ 3 score and will include two parts: the execution of the tasks by the child and the filling

of the questionnaire by the guides. For each child, the performance will only last between 10 to 15 minutes. The results of the assessment of psychomotor development are listed in the corresponding item.

The practical modalities of the DPM evaluation as well as the corresponding items are given in the appendix to this protocol (appendix 3).

For the children who will be selected for the Sub-study on psychomotor development, their anthropometric measurements (weight, height, MUAC, search for edema) will be taken during a visit after treatment when they respond to the appointments for the evaluation of the patient. psychomotor development: at the end of treatment (for children declared cured) then at six months. This information will be noted in their corresponding individual monitoring sheet.

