### 2.1.3.Intervention

As part of the EfRAMAS project, the intervention will consist of the management of SAM with all the care provided for in the national protocol. The only difference will be in the dosage of RUTF over time. Both groups will receive the same dose of RUTF for the first two weeks. Then in the intervention group, the reduction in the dose of RUTF will take place from the third week of treatment (Table 2). The intervention will begin concomitantly in both groups.

Chart 2 : Dose of RUTF per group in number of sachets per week

| Weight (kg) | Standard dose control group |               | Reduced dose intervention group |               |                    |               |
|-------------|-----------------------------|---------------|---------------------------------|---------------|--------------------|---------------|
|             | Admission-Discharge         |               | Weeks 1-2                       |               | Week 3 - discharge |               |
|             | Bags / week                 | Kcal / kg / d | Bags / week                     | Kcal / kg / d | Bags / week        | Kcal / kg / d |
| 3.0-3.4     | 9                           | 168-190       | 9                               | 168-190       | 7                  | 147-167       |
| 3.5 - 4.9   | 11                          | 183-204       | 11                              | 183-204       | 7                  | 102-143       |
| 5.0 - 6.9   | 14                          | 155-214       | 14                              | 155-214       | 7                  | 72-100        |
| 7.0 - 9.9   | 21                          | 144-204       | 21                              | 144-204       | 14                 | 101-143       |
| 10.0 - 14.9 | 28                          | 144-214       | 28                              | 144-214       | 14                 | 67-100        |

When a participant does not respect his date of appointment, the day he presents for the consultation, he will receive the number of sachets in proportion to the number of days remaining before the next appointment.

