##### b. Additional results

The additional results expected in this study, in the two groups (control and intervention), are:

- **The duration of the edema melting:** calculated in number of days, this indicator corresponds to the time taken for the lower limbs of SAM children to return to their normal volume. The expected result is the onset of melting of the edemas within the first 14 days after admission and their complete disappearance after 21 days of treatment.
- **The length of stay:** calculated in number of days, this indicator corresponds to the time elapsed between admission and discharge ( $PB \geq 12.5\text{cm}$  and / or  $PT \geq -3$  Z score and / or edema melt). The maximum length of stay is 12 weeks or 3 months(12).
- **The cure rate:** A child will be considered cured if he meets the cure criteria according to his admission category: A  $PT \text{ index} \geq -1.5$  or  $PB \geq 125 \text{ mm}$  during two consecutive visits and no edema during two visits (2 consecutive weeks).
- **The dropout rate:** it is the proportion of children confirmed alive who missed two successive visits. The abandonment is confirmed once after the visit of the RECO which confirms that the child is alive despite his 2 absences during the weekly visits. Children who have abandoned will be followed up to 3 months after the abandonment. For children who can be found, offer the caregivers a small snack at the single appointment 3 months after abandonment to take the anthropometric measurements.
- **Death rate :** the proportion of children randomized to the study who died during the intervention at any time.
- **Cost savings** (average cost saved and cost saved per child treated): this involves comparing the cost of treatment for children in care and declared cured in the two groups. We will use a societal perspective including the direct costs of drugs and RUTF

(purchase, transport, transport and storage) to assess the cost for each child, the HR costs involved in the care, the non-medical costs (food and transport. beneficiaries), indirect costs (loss of productivity).

- The growth velocity of the anthropometric variables and indices: it will be a question of evaluating the prevalence of stunting, underweight of the children included in the study in the two groups at the end of the treatment.

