### **2.2.2. Randomization concealment mechanisms**

Once the randomization lists are generated, they will be printed and kept in two copies, one at the ACF headquarters in Paris and the other at the ESP in Kinshasa. The randomization list for each UNTA will be sent by sealed envelope to the nurse in charge of the corresponding health area (IT). Researchers will not have access to the footage. Only ITs will have access to the randomization sequences of the corresponding UNTA.

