### **2.2.3. Implementation**

Randomization will be done using [www.randomization.com](http://www.randomization.com) by an independent person who will not participate in the implementation of the study. Study participants will be recruited from the 14 UNTAs (due to 7 per ZS) selected and upon admission each will receive a unique identifier corresponding to their group in the study. The IT will receive special training to enable it to know how to randomly assign the identifier to UNTA participants.

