### **2.2.4. Blinding (masking)**

The statistician who will do the randomization will send the results in closed envelopes which will only be opened by the ITs of each selected UNTA. Neither the nurses who will take the anthropometric measurements nor the researchers will know which group each child

participating in the study belongs to. Due to the differing amounts of total RUTF sachets distributed, parents may deduct the dose their children will receive and thus not be blinded.

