### b. Data collection plan

| Frequency of data collection                   | Admission | Weekly treatment max 12 weeks | Dump | Monthly follow-up +3 months after discharge | Monthly follow-up at +6 months after discharge |
|------------------------------------------------|-----------|-------------------------------|------|---------------------------------------------|------------------------------------------------|
| Selection for inclusion in the study           | X         |                               |      |                                             |                                                |
| Information, consent and randomization         | X         |                               |      |                                             |                                                |
| Sociodemographic questionnaire                 | X         |                               |      |                                             |                                                |
| Physical examination                           | X         | X                             | X    |                                             |                                                |
| Anthropometric measurements                    | X         | X                             | X    | X                                           | X                                              |
| Distribution of RUTF                           | X         | X                             |      |                                             |                                                |
| Psychomotor Development Score (DPM) Assessment | X         |                               | X    |                                             | X                                              |
| Individual interview for acceptability study   |           |                               |      |                                             |                                                |
| FGD                                            |           |                               |      |                                             |                                                |

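### Death, transfer and drop-out are compared between arms only from admission, although the arms are treated alike until week 3; a prespecified week-3-onward comparison should stand beside the ITT one.

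*Protocol*

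**What the plan says.** Allocation happens at admission. The schedule in Protocol 2.3.1 b puts "Information, consent and randomization" in the admission column, section 2.3.1 f (At UNTA level) says "If consent is obtained, the nurse assigns an ID to the child that matches the randomization ID", and section 2.2.3 adds that "upon admission each will receive a unique identifier corresponding to their group in the study".

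The treatments separate later. Chart 2 in section 2.1.3 gives both arms the same sachets in weeks 1-2, and in the intervention group "the reduction in the dose of RUTF will take place from the third week of treatment".

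The harm indicators run from admission. Section 2.1.4 b defines the death rate as "the proportion of children randomized to the study who died during the intervention at any time". Annex 8 takes transfer to hospital over the three months of treatment, and takes transfer, death and drop-out over all children followed in each arm. Section 2.3.3 analyses secondary results by ITT only and calls a difference significant at p below 0.05. The secondary hypotheses expect the performance indicators to be the same in both arms. No indicator is counted from week 3.

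**The concern.** A child who dies or is transferred in the first two weeks had the same ration whichever arm was assigned. Such events should occur at about the same rate in both arms. They add counts to both sides without carrying information on the reduced dose, so a real excess from week 3 looks smaller as a ratio and is estimated less precisely.

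The direction matters. The protocol hopes to show that the indicators are the same and judges differences by a significance test. A non-significant result is then easily read as support, and anything that makes the test less sensitive works in favour of the reduced dose. Death and transfer are the outcomes on which readers will judge whether cutting the ration in severely malnourished children was safe.

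**Working it through.** **The plan's own figure.** Section 2.1.6 gives 335 per group. With its rounded z values, (1.64 + 0.84)² × 2 × 2.6² / 0.5² = 6.1504 × 13.52 / 0.25 = 332.6; with unrounded z values the result is 335. The figure reproduces and is not disputed. It sizes the trial on weight gain, not on death or transfer.

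**Inputs.** From the protocol: 500 children per arm (Annex 5), identical treatment in weeks 1-2, and a 5% significance level (taken as two-sided). Assumed, because the protocol gives no such rate: 5% of control children have the event over the whole stay; a share f of those events falls in weeks 1-2 at the same rate in both arms; the reduced dose doubles the later risk.

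**Rates.** Let e = 0.05f (early) and l = 0.05 − e (later).
- From admission: control e + l, reduced e + 2l.
- From week 3: control l/(1 − e), reduced 2l/(1 − e).

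**Power.** Φ[(d − 1.96·se₀)/se₁], where d is the risk difference, se₀ = √(2p̄(1 − p̄)/n) and se₁ = √([p₁(1 − p₁) + p₂(1 − p₂)]/n).

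**Worked case, half early.**
- From admission, n = 500: 5.0% v 7.5%, d = 0.025, p̄ = 0.0625, se₀ = 0.01531, se₁ = 0.01529. (0.025 − 1.96 × 0.01531)/0.01529 = −0.33, so power is 37%.
- From week 3, n = 475 (5% gone for any reason): 2.56% v 5.13%, d = 0.0256, p̄ = 0.0385, se₀ = 0.01248, se₁ = 0.01245. (0.02564 − 1.96 × 0.01248)/0.01245 = 0.09, so power is 54%.

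The risk difference hardly moves (2.5 v 2.6 points). The risk ratio goes from 1.5 to 2.0, and the standard error falls from 1.53 to 1.25 points.

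**All cases.** The week-3 power range runs from n = 475 to n = 500(1 − e), where only the early events themselves are removed.

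| Control events | Share early | Ratio, from admission | Risk difference, admission / week 3 (points) | Power, admission | Power, week 3 |
|---|---|---|---|---|---|
| 5% | 50% | 1.5 | 2.5 / 2.6 | 37% | 54-55% |
| 5% | 30% | 1.7 | 3.5 / 3.6 | 60% | 68-70% |
| 5% | 10% | 1.9 | 4.5 / 4.5 | 78% | 79-81% |
| 10% | 50% | 1.5 | 5.0 / 5.3 | 67% | 85% |
| 10% | 30% | 1.7 | 7.0 / 7.2 | 90% | 95% |

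**A second parameterisation.** Fix the later risk at 5% v 10% among children who reach week 3, and add early exits equal in both arms. With 5% early exits, the rates from admission are 0.05 + 0.95 × 0.05 = 9.75% and 0.05 + 0.95 × 0.10 = 14.5%. The ratio is 1.49, the difference 4.75 points and power 63%. From week 3 with 475 per arm, power is 83%. The direction is the same; the size depends on how common early events are.

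**The case against.** The protocol compares strategies that start at admission, and ITT from admission is unbiased for that comparison. The absolute excess is nearly preserved. A reader might infer that the plan conceals harm or that its ITT count is wrong; neither follows. The trial is not sized on these outcomes, and in the worked case the week-3 comparison is still underpowered at 54%.

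A large early share is also doubtful for some outcomes. Chart 3 declares drop-out only in the third week of absence. Two transfer triggers in section 2.1.3 a (weight loss over two consecutive weeks, stagnation at three consecutive weighings) cannot be met before about day 14. If only 10% of events are early, little is gained.

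A reader might go further and ask for randomisation to move to week 3. That is a trade-off, not a correction. Section 2.2.2 says "Only ITs will have access to the randomization sequences of the corresponding UNTA", so the nurse holding the list would allocate after seeing two weeks of response, and melting of edema, expected to begin within 14 days, would partly precede allocation.

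A reader might also infer that early knowledge of the arm distorts tracing and sub-study selection. The dispenser "will know who receives the reduced dose according to the IDs of the children", but section 2.3.1 f says that this provider does not follow the children up. Home tracing falls to the community relays (2.1.3 c), and sub-study selection uses a fixed step (Annex 3). Section 2.2.4 intends that "Neither the nurses who will take the anthropometric measurements nor the researchers will know which group each child" belongs to. The nurses' task list in section 2.3.1 does blur these roles, but that is a separate masking question that lasts the whole treatment.

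Finally, a SAP, which was not available, could hold a week-3 analysis. The protocol itself, however, fixes the counting window for death and restricts secondary results to ITT, so the addition belongs in its text.

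**Conclusion.** The point stands as a loss of sensitivity. Early events that the dose cannot have caused move the risk ratio towards 1 and widen the interval, while the ITT comparison remains valid and the risk difference is nearly unchanged. Under a doubled later risk, 5% control events and 500 per arm, counting from week 3 raises power by about 17 points if half the control events are early, about 9 points if 30% are, and about 2 points if 10% are. These sizes rest on assumed event rates and timing; only the direction follows from the design. The data needed are already collected weekly, so the improvement is worth making even if the gain proves small.

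**What to change.** Keep randomisation at admission and keep every ITT indicator as defined. Add to section 2.3.3 a prespecified between-arm comparison of death, transfer to UNTI and drop-out, counted from the visit at which the week-3 ration is due, among children still in treatment then.

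- Define that visit by the same rule in both arms, since control children have no change of ration to mark it.
- Date drop-out by the first missed visit. Dated by declaration, children who stopped attending in weeks 1-2 would be counted as later events.
- Report weeks 1-2 events separately by arm, as a check that they are balanced.
- Give the risk difference and the risk ratio with confidence intervals for both counts.

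The cost is a little more analysis work, with no new data and no change to treatment or allocation. The comparison is conditional on reaching week 3. If weeks 1-2 events turn out unbalanced it could itself be biased, which is why it sits beside the ITT result and does not replace it.
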